## Abstract

**Background:**

Hand hygiene prescriptions are the most important measure in the prevention of hospital-acquired infections. Yet, compliance rates are generally below 50% of all opportunities for hand hygiene. This study aims at evaluating the short- and long-term effects of two different strategies for promoting hand hygiene in hospital nurses.

**Methods/design:**

This study is a cluster randomised controlled trial with inpatient wards as the unit of randomisation. Guidelines for hand hygiene will be implemented in this study. Two strategies will be used to improve the adherence to guidelines for hand hygiene. The state-of-the-art strategy is derived from the literature and includes education, reminders, feedback, and targeting adequate products and facilities. The extended strategy also contains activities aimed at influencing social influence in groups and enhancing leadership. The unique contribution of the extended strategy is built upon relevant behavioural science theories. The extended strategy includes all elements of the state-of-the-art strategy supplemented with gaining active commitment and initiative of ward management, modelling by informal leaders at the ward, and setting norms and targets within the team. Data will be collected at four points in time, with six-month intervals. An average of 3,000 opportunities for hand hygiene in approximately 900 nurses will be observed at each time point.

**Discussion:**

Performing and evaluating an implementation strategy that also targets the social context of teams may considerably add to the general body of knowledge in this field. Results from our study will allow us to draw conclusions on the effects of different strategies for the implementation of hand hygiene guidelines, and based on these results we will be able to define a preferred implementation strategy for hospital based nursing.

**Trial registration:**

The study is registered as a Clinical Trial in ClinicalTrials.gov, dossier number: NCT00548015.

## Background

Hospital-acquired infections (HAIs) are a serious and persistent problem throughout the world. They are burdensome to patients, complicate treatment, prolong hospital stay, increase costs, and can be life threatening [1,2].

Micro-organisms on the hands of healthcare workers contribute to the incidence of infections in patients [3,4]. Therefore, hand hygiene prescriptions are widely accepted as the most important measure in the prevention of HAIs [5-11]. Unfortunately, numerous studies over the past few decades have demonstrated that healthcare workers still perform hand hygiene on average less than 50 percent of the times required [12-14]. Thus, current practices deviate from the goal of providing safe hospital care aimed at prevention of adverse events, morbidity, and mortality.

In their review on approaches for transferring evidence to practice, Grol and Grimshaw [15] used a case study looking at strategies to improve hand hygiene in hospital settings. They concluded that plans for improvement of current performance should be based on barriers and facilitators for change. Regarding hand hygiene, they concluded that changing behaviour is possible, but this change generally requires 'a comprehensive plan with strategies at different levels (professional, team, patient, and organisation) to achieve lasting changes in hand hygiene routines.'

Traditionally, implementation strategies have focussed on professionals--the individual level--or addressed structural work context--the organisational level. Team-directed strategies are hardly studied [15,16]. Yet, team-directed strategies could be valuable as healthcare workers (especially nurses) usually work in teams. Performing and evaluating an implementation strategy that also targets the social context of teams may considerably add to the general body of knowledge in this field.

### Aims and objectives

The aim of this study is to test two implementation strategies in inpatient wards to improve nurses' compliance with hand hygiene prescriptions and to compare the short-term and sustained effects of these innovative strategies. The objectives of this project are threefold: to improve compliance with guidelines for hand hygiene in nurses; to assess the cost effectiveness of both strategies; and to gain insight into determinants of success or failure of the strategies.

### Scientific hypothesis

Our hypothesis is that an extended strategy, using additional implementation activities based on social influence and leadership, will be more effective in increasing hand hygiene compliance rates compared to a state-of-the-art strategy, mainly addressing the individual and organisational level.

## Methods

### Quality improvement strategies

The state-of-the-art strategy is based on current evidence from literature on hand hygiene compliance [1,15]. Short-term effectiveness of this strategy is well-established in several studies and settings [16,17]. The strategy includes: education for improving relevant knowledge and skills; reminders for supporting the transfer from a positive intention to the actual performance of hand hygiene; feedback as a means to provide insight into current hand hygiene behaviour and to reinforce improved behaviour; and screening for adequate hand hygiene products and adequate facilities. The extended strategy also contains activities based on social influence in groups and leadership. This strategy largely draws from relevant theories and general evidence to support these theories [18-26]. The extended strategy includes all of the above elements of the state-of-the-art strategy as well as: gaining active commitment and initiative of ward management; modelling by informal leaders at the ward; and setting norms and targets within the team. Table 1 shows the operationalisation of both strategies.

**Table 1 T1:** Description implementation strategies

State-of-the-art strategy	Extended strategy
**Education**	**All elements of the state-of-the-art strategy**
Distribution of educational material/written information (leaflet) about hand hygiene	• Education, reminders, feedback, facilities and products
• The importance of hand hygiene	**Setting norms and targets within the team**
• Misconceptions about alcohol-based hand disinfection	• Three interactive team sessions that includes goal setting in hand hygiene performance at group level
• Theory and practical indications for the use of hand hygiene	• Analysis of barriers and facilitators to determine how they could best adapt their behaviour in order to reach their goal
Website http://www.gewoonhandenschoon.nl	• Nurses address each other in case of undesirable hand hygiene behaviour
• Educational material/written information about hand hygiene	**Gaining active commitment and initiative of ward management**
• Knowledge quiz	• Ward manager designates hand hygiene as a priority
• Reward for the nursing ward with the most visitors to the website	• Ward manager actively supports team members and informal leaders
Educational sessions on prevention of hospital acquired infections	• Ward manager discusses hand hygiene compliance rates with team members
• Launching hospital wide campaign with practical demonstrations of hand hygiene	**Modeling by informal leaders at the ward**
**Reminders**	• Informal leaders demonstrate good hand hygiene behaviour
• Distribution of posters that emphasized the importance of hand hygiene, particularly alcohol-based hand disinfection	• Informal leaders models social skills in addressing behaviour of colleagues
• Interviews and messages in newsletters or hospital magazines	• Informal leaders instruct and stimulate their colleagues in providing good hand hygiene behaviour
• General reminders by opinion leaders/ward management	
**Feedback**	
• Bar charts of hand hygiene rates of every nursing ward will be sent to the ward manager twice	
• Comparison ward performance and hospital performance	
**Facilities and products**	
• Screening and if necessary adapt products and appropriate facilities	

### Study design

The study will have a stratified cluster randomised trial design. In a cluster randomised trial, groups of individuals rather than individuals are randomised [27]. Cluster randomisation using wards as the unit of allocation reduces contamination between groups [28]. In our study, the quality improvement strategies involved the entire team of nurses and not individual nurses on nursing wards. Therefore, nurses within the same ward were considered to be a cluster.

Data will be collected for a six-month reference period--no strategy for promoting hand hygiene--prior to the trial (T1 and T2). After data collection for this reference period, randomisation to either the state-of-the-art strategy or the extended strategy will take place. Strategies will be delivered during a second period of six months. Follow-up measurements will take place directly after strategy delivery (T3) and at six months after the end of strategy delivery (T4). Because the extended strategy consists of the state-of-the-art strategy supplemented with team-directed social influence approaches, randomisation of wards to each of the strategies is feasible. Our study design is illustrated in figure 1.

**Figure 1 F1:**
[figure not shown]

### Setting and participants

The study will be performed in three hospitals: one university medical centre and two general hospitals. In a fourth (non participating) hospital, we will test the instruments and observer variability. Within the hospitals, all inpatient wards (n = 60), will participate in the study.

After completing baseline measurements of the reference period, wards will be randomly assigned to either the state-of-the-art strategy group (n = 30), or the extended strategy group (n = 30). The randomisation of the wards will be stratified for type of ward to minimize differences in ward characteristics over the strategies. We will randomise surgical wards, internal medicine wards, intensive care units, and paediatric wards.

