### Statistical analysis

The effects of the two strategies will be evaluated on an intention-to-treat basis by comparing the hand hygiene compliance rates in the two study groups after performing the strategies with the compliance rates at the end of the reference period. The differences between the two strategies will be evaluated by comparing the hand hygiene compliance rates of both groups after performing the strategies. Multilevel analysis will be applied to compensate for the clustered nature of the data (compliance is clustered within healthcare workers who are clustered within units) using mixed linear modelling techniques, including the following covariates: ward (random effect), HCW (random effect, nested within ward), institution and the baseline results of the wards. The relevance of nurses' gender, ward specialism, and type of hand hygiene opportunity will also be explored by performing sub group analyses.

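### All 60 wards are randomised after baseline is measured, yet only ward type is balanced; constraining the draw on hospital and baseline compliance would cheaply recover some precision

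*Protocol article*

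**What the plan says.** Under Setting and participants, the article says that "all inpatient wards (n = 60), will participate in the study", in three hospitals: one university medical centre and two general hospitals. Allocation is 30 wards to each strategy. Study design fixes the timing: "After data collection for this reference period, randomisation to either the state-of-the-art strategy or the extended strategy will take place". Setting and participants repeats it: "After completing baseline measurements of the reference period, wards will be randomly assigned".

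The balancing rule is a single sentence: "The randomisation of the wards will be stratified for type of ward to minimize differences in ward characteristics over the strategies". The strata follow: "We will randomise surgical wards, internal medicine wards, intensive care units, and paediatric wards". No other balancing factor is named.

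The Statistical analysis section for hand hygiene compliance specifies a mixed model with ward and healthcare worker as random effects. Its further covariates are "institution and the baseline results of the wards". Ward type is not a listed covariate; ward specialism appears only among the exploratory subgroup analyses.

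**The concern.** The balancing rule is meant to make ward characteristics alike across the strategies. The two ward-level characteristics that the authors consider important enough to adjust for are hospital and baseline compliance. Both are known for every ward when the single draw is made, yet the rule leaves both to chance.

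When arm and covariates are correlated by chance, the model has to separate them, and the strategy estimate loses precision. The number of wards is fixed at all those available, so this loss cannot be made up by adding wards. It can be avoided only before the draw. The article states the balancing factor explicitly, so this is a comment on a stated choice and not on a detail left to a fuller protocol.

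**Working it through.** **The plan's own figure.** Sample size gives 80% power, two-sided alpha 0.05, a ward ICC of 0.05, a nurse ICC of 0.6, and 50 observations from 15 nurses in each of 60 wards. The effects are 15 points for the state-of-the-art strategy and 10 more for the extended one. With m = 50 and k = 50/15 = 3.33 observations per nurse, two three-level design effects are plausible:

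- Additive: 1 + (3.33 − 1) × 0.6 + (50 − 3.33) × 0.05 = 4.73.
- Product: [1 + (3.33 − 1) × 0.6] × [1 + 14 × 0.05] = 4.08.

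The article gives no exact baseline rate. With the product form, 80% is reproduced at an assumed baseline of about 40–43% (79.2–80.3%). With the additive form it is reproduced at about 50–52% (78.6–80.2%). So 80% is attainable and is used below as the nominal level.

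**Cost of imbalance.** Arm, hospital and baseline all act at ward level. Let R² come from regressing arm on the covariates over the 60 wards. The variance of the adjusted strategy difference is multiplied by 1/(1 − R²), and the share of information lost is R². Under random allocation R² follows approximately Beta(d/2, (N − d)/2). Here d = 3 (two for hospital, one for baseline), or 4 if T1 and T2 both enter. N = 59, or 56 once the four ward-type means are removed.

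| Covariates | Mean information loss | 95th percentile | Mean variance inflation | 95th percentile |
|---|---|---|---|---|
| Hospital + one baseline (d = 3) | 5.1–5.4% | 12.9–13.6% | 5.6–5.9% | 14.8–15.7% |
| Hospital + T1 and T2 (d = 4) | 6.8–7.1% | 15.6–16.4% | 7.5–8.0% | 18.5–19.6% |

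For example, with d = 3 and N = 56, mean loss = 3/56 = 5.4% and mean inflation = 3/(56 − 3 − 2) = 5.9%.

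**Check by simulation.** The draws were 30:30 and balanced within ward type only. Assumed hospital splits were 20/20/20, 30/15/15, 36/12/12 and 40/10/10 wards, with several assumed splits by type. With one baseline covariate, mean inflation was about 6% and the 95th percentile about 15–16% throughout, so the unknown ward counts hardly matter.

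**After constraining the draw.** Two forms of constraint were tried, each with one baseline covariate:

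- Each arm within one ward of half of each hospital, and a baseline gap under 2 points: mean inflation 0.5–0.9%, 95th percentile 0.9–1.5%. About 8–15% of type-balanced allocations qualify, so the choice of allocations stays wide.
- Drawing from the best tenth of type-balanced allocations: mean loss 0.6%, 95th percentile 1.3%.

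**Power.** Take 80% as the power with no adjustment and no imbalance. Let r be the ward-level correlation between baseline and follow-up. Adjusting multiplies the variance by (1 − r²) × V, where V is the inflation factor. Power = Φ(2.80/√[(1 − r²)V] − 1.96).

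| r (assumed) | Constrained draw | Average type-only draw (V ≈ 1.06) | Worst 1 in 20 (V ≈ 1.15) |
|---|---|---|---|
| 0 | about 80% | about 78% | about 74% |
| 0.3 | about 83% | about 81.5% | about 78% |
| 0.5 | about 90% | about 88% | about 85% |

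Across rows, the average draw loses about 1.5–2 points against a constrained one, and the worst one in twenty loses about 4.5–6. The average loss is offset by adjustment once r² exceeds 1 − 1/1.06, that is r above about 0.24. A 15% inflation is offset once r² exceeds 1 − 1/1.15, r about 0.36.

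**The case against.** The strongest reply is that stratifying on ward type and adjusting for hospital and baseline is a valid, internally consistent plan. The article contradicts nothing here. That stands, and it is why this is an improvement and not an error.

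A reader might go further in four ways that the article does not support:

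- **The trial falls short of 80% power.** The sample size shows no credit for baseline adjustment. Charging it with the cost of adjusting while ignoring the gain is one-sided. The 78% and 74% figures apply only if baseline predicts nothing. The article does not give r, so only the range can be stated.
- **Imbalance biases the strategy comparison.** It does not, because the planned model includes both factors.
- **The before-after effects of the two arms cannot be compared if hospital mixes differ.** Each arm is compared with its own rates at the end of the reference period, so stable hospital differences cancel. Hospital mix would matter only if hospitals responded differently, which the article does not say.
- **The arms will often start far apart.** Take an assumed variance of observed ward rates of 0.0239. The standard error of the T2 difference is then √(0.0239 × 2/30) = 0.040, and a gap above 5 points arises in about 21% of draws. But 0.0114 of that variance is observation error. For stable ward differences alone (0.0125) the standard error is 0.029 and the figure about 8%.

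The inflation figures of 6% and 15% should also not be read as information lost; with one baseline covariate that is about 5% and 13–14%.

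What remains is a real relative advantage for a constrained draw at every r.

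**Conclusion.** The point holds as a cheap improvement. Balancing on ward type alone inflates the variance of the adjusted strategy difference by about 6% on average and by about 15% or more in one draw in twenty, somewhat more if T1 and T2 both enter the model. A constrained draw brings the average to under 1% with one baseline covariate. The average gain is modest; the main benefit is protection against an unlucky single draw that cannot be repeated.

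The result assumes equal ward sizes and assumed ward counts per hospital and type, to which it is insensitive. The power figures also assume a nominal 80% and the stated range of r.

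**What to change.** In Setting and participants, replace stratification on ward type alone with covariate-constrained randomisation:

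1. Consider 30:30 allocations balanced within ward type.
2. Keep those in which each arm is within one ward of half of each hospital and the arms differ little in mean baseline compliance (for example, by under 2 points).
3. Draw one of these at random.

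In the Statistical analysis section for compliance, keep institution and baseline in the model and add ward type, because it constrains the draw.

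Stratifying on type by hospital without baseline would be a partial remedy: mean information loss about 2–3%, 95th percentile 7–8%.

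The cost is about half a day of programming, and T2 data must be cleaned before the draw. Wards, staff and measurements do not change.

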### Parameters, instruments, and analysis

To evaluate the effectiveness and efficiency of the strategies, we will use effect parameters and process parameters. First, we describe the evaluation of hand hygiene compliance and team climate. Second, the economic evaluation regarding costs and health effects. Finally, we describe the assessment of the actual implementation of the strategies and the evaluation of barriers and ward structure.

### Effect evaluation: hand hygiene compliance

Table 2 presents the effect parameters and instruments. The primary effect parameter for this study is the percentage of opportunities at which hand hygiene is performed by the nurses according to the National Guideline 'Handhygiene' of the Working group Infection Prevention (WIP) and the WHO Guidelines on Hand Hygiene in Healthcare [29,30]. The indications that create an opportunity--a required moment--for hand hygiene are listed in Table 3. Hand hygiene is operationalised as 'hand washing with either plain soap and water' or 'hand disinfection through the use of an alcohol-based hand rub solution.'

**Table 2 T2:** Parameters and instruments

Effect parameter	Description	Instruments
Hand hygiene compliance Other parameters	The percentage of opportunities at which hand hygiene was performed according to the National Guideline 'Handhygiene' of the Working group Infection Prevention (WIP) and the WHO Guidelines on Hand Hygiene in Healthcare The percentage of presence of jewelry and long-sleeved clothes	Hand hygiene monitoring tool

Team Climate	Dimensions 'participation safety,' 'task orientation,' support for innovation,' and 'interaction.'	Team Climate Inventory

Costs and health effects	Comparing resource consumption and HAIs rate between the two implementation strategies	Activity-based costing; Decision analysis

**Process parameter**	**Description**	**Instruments**

Performance of the strategies	*State-of-the-art strategy *- Knowledge - number of nurses that completed the knowledge quiz, presence of instruction leaflets. - Reminders - check of presence of posters. - Performance feedback - actual delivery of performance feedback to team members.	Survey, direct observations; systematic registration of time and meeting minutes
	Extended strategy - Coaching of ward management- number of coaching sessions, total time spent on coaching, topics dealt with, managers evaluations of coaching. - Coaching of informal leaders - number of coaching sessions, total time spent on coaching, topics dealt with, informal leaders evaluations of coaching. - Team discussions for norm- and target setting - number of nurses attending per ward, time investment per ward, actual norms and targets decided on, nurses' evaluations of team discussions	

Barriers to change	Including determinants like awareness, knowledge, reinforcement, control, social norms, leadership, and facilities	Barrier questionnaire

Ward structure	Information about existing structures and resources like actual presence of facilities, workload, nurse-bed ratio -under-staffing and support from the management	Ward structure questionnaire

**Table 3 T3:** Observed indications for hand hygiene

Indication for hand hygiene	When	Transmission risk	Major targeted negative infectious outcome	Examples
Before an aseptic task	Directly before performing an aseptic task	Hand transmission of micro-organisms from any surface (including the patient skin) to a site that would facilitate invasion and infection	Endogenous or exogenous infection of the patient	Giving an injection. Insertion and care of intravenous catheters. Blood draws. Administering intravenous medication. Endotracheal suction

From contaminated body site to another body site	Directly after completing task (whether gloved or ungloved)	Hand exposure to patient's contaminated body sites and fluids potentially containing blood-borne or other pathogens	Infection of the HCW by patient blood borne pathogens	Drawing blood and then adjusting the infusion drop count. Handle wound, mucous membrane, and body fluids. After oral care

After touching the patient	Directly after leaving the patient when the patient was touched	Hand transmission of micro-organisms from the patient flora to other surfaces in the healthcare setting	Dissemination of patient flora to the rest of the healthcare environment and infection of other patients or HCWs	After skin contact with the patient. Bathing, change position or lifting a patient. Taking a pulse or blood pressure. Shaking hands

After taking care of an infected/colonized patient	Directly after leaving the patient's room	Hand transmission of micro-organisms from the patient flora to other surfaces in the healthcare setting	Dissemination of patient flora to the rest of the healthcare environment and infection of other patients or HCWs	Contact with any patient know to be infectious/isolated (eg. MRSA)

After use of gloves	Directly after removing gloves	Hand transmission of micro-organisms from the skin of the HCW 's to other surfaces in the healthcare setting	Dissemination of patient flora to the rest of the healthcare environment and infection of other patients or HCWs	Wearing gloves high-risk contacts

After contact with patient surroundings	After completing the task and before contacting another patient	Hand transmission of micro-organisms from the patient flora to other surfaces in the healthcare setting	Dissemination of patient flora to the rest of the healthcare environment and infection of other patient or HCWs	Touching the patient's environment like bed, table, blanket, clothes. After contact with medical equipment in the immediate vicinity of the patient

Other effect parameters are the presence of jewelry (ring, watch, or other jewelry) and whether the nurses wear long-sleeved clothes under their short-sleeved uniforms. We will observe compliance by using a Hand Hygiene Monitoring Tool adapted from the WHO (additional file 1). The observer will register each opportunity in a corresponding column block, note all of the applicable indications and whether hand hygiene is performed by hand disinfection or hand washing or is missed.

